### 3. METHODS AND PROCEDURES

#### 3.1 Study

##### Design

The proposed study is a 3-arm RCT of 12 months duration. Participants will be randomized with equal allocation to

| Intervention Components (rows) and Groups (columns)                      | CONTROL | VIDEO | VIDEO+CHW |
|--------------------------------------------------------------------------|---------|-------|-----------|
| Standard of T2D care                                                     | X       | X     | X         |
| 1 DSMES video/week for 24 weeks                                          |         | X     | X         |
| Bi-weekly phone calls from CHWs on addressing SDOH barriers for 24 weeks |         |       | X         |

Table 1. Intervention Components (rows) and Groups (columns)

one of 3 arms (n=135 each): 1) wait-list control (hereafter CONTROL); 2) video-based DSMES intervention (hereafter VIDEO); or 3) video-based DSMES+CHW intervention (hereafter VIDEO+CHW). All of the groups will continue to receive standard of care treatment for their T2D. The VIDEO group will receive 1 brief DSMES video per week for a total of 24 weeks. The VIDEO+CHW group will receive the same DSMES videos plus bi-weekly support calls from a trained CHW for 24 weeks. The CONTROL group will continue to receive their standard of care for T2D during the study duration and at the end of the study, they will be provided the opportunity to receive DSMES videos.

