**Sample Size Estimates: Primary Outcome (HbA1c at 6 months):** The primary aim is to examine the efficacy of the VIDEO and VIDEO+CHW interventions on HbA1c (primary outcome) at 6 months. We hypothesize that the VIDEO+CHW group will have the largest reduction in HbA1c, followed by the VIDEO group and then the CONTROL group at 6 months ( $HbA1c_{VIDEO+CHW} < HbA1c_{VIDEO} < HbA1c_{CONTROL}$ ). Based on our preliminary data, we expect to observe a 0.6% difference between the VIDEO and CONTROL groups. Based on data of a prior CHW intervention in Hispanic immigrants with T2D, we expect to see a group difference of 0.4% between the VIDEO+CHW and VIDEO groups. Using the observed  $SD=0.8\%$  of HbA1c in our preliminary study, based on a two-sample two-sided t-test,  $n=86$  (per group) will be required to detect a minimum group difference of 0.4% in HbA1c with a power of 80% and a type I error of 0.0167 (to account for 3 group comparisons). We will abstract HbA1c data from the electronic medical record, which often has a high rate of missing data due to various reasons (e.g., patients miss the A1c appointment or change to a different health care system). Our pilot study achieved 70% completion rate of A1c follow up data. With a conservative rate of 60-65%, we will recruit 405 (135/group) participants to yield a final sample of at least 258 (86/group). We believe a sample of 405 will provide sufficient power to detect significant differences between the three groups (VIDEO+CHW vs. VIDEO; VIDEO vs. CONTROL; VIDEO+CHW vs. CONTROL).

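### The stated minimum of 86 per group is not reached at the lower part of the protocol's own 60–65% completion range: 60% leaves 81 per group and about 78% power for the 0.4% contrast

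*Protocol*

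**What the plan says.** Protocol Section 3.2 (Sample and Sites, paragraph on sample size estimates) builds the sample size in two steps.

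- **Evaluable sample.** The calculation is "based on a two-sample two-sided t-test" with SD 0.8% and "a type I error of 0.0167 (to account for 3 group comparisons"). From this, 86 per group "will be required to detect a minimum group difference of 0.4% in HbA1c with a power of 80"%. The 0.4% is the difference expected between VIDEO+CHW and VIDEO. For the other adjacent pair, "we expect to observe a 0.6% difference between the VIDEO and CONTROL groups".
- **Recruited sample.** The paragraph explains that HbA1c taken from medical records is often missing, cites 70% completion in the pilot, and plans below that: "With a conservative rate of 60-65%, we will recruit 405 (135/group) participants to yield a final sample of at least 258 (86/group"). Section 3.1 gives the same allocation: "one of 3 arms (n=135 each").

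The paragraph ends by claiming adequate power for all three pairwise comparisons.

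**The concern.** The sentence derives a minimum from a range of completion rates. A minimum has to hold at the worst rate in the range, here 60%. It does not: the 86 per group belongs to a rate in the upper part of the range.

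This matters because the calculation has almost no slack. The 86 per group gives just over 80% power for the contrast that sets the sample size, VIDEO+CHW against VIDEO. Section 3.1 presents that contrast as the test of what CHW support adds to the videos. Any yield below 86 takes its power under the stated 80%, and a reader relying on the word "conservative" in the protocol's sentence would assume that the low end had been covered.

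**Working it through.** **Inputs, all from Protocol Sections 3.1 and 3.2.** Difference 0.4% (0.6% for VIDEO vs CONTROL); SD 0.8%; two-sided alpha 0.0167 per comparison; two-sample t-test; 80% power; 135 recruited per group; completion 60–65%; pilot completion 70%.

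**Step 1: reproduce the 86.** Standardised difference d = 0.4/0.8 = 0.5. For n per group, the t-test has 2n − 2 degrees of freedom and noncentrality d × √(n/2). Solving for 80% power gives n = 85.2, so 86 per group, as stated. Power at 86 is 80.4%; at 85 it is already 79.9%. The normal approximation gives 84.

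**Step 2: completion needed for the stated minimum.** 86/135 = 258/405 = 63.7%. The claim therefore fails from 60% up to about 63.7%, which is 3.7 of the 5 points in the range.

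**Step 3: yield and power across completion rates.** Yield per group = 135 × rate; power is from the noncentral t at that yield. Fractional yields are kept.

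| Completion | Per group | Total | Power, 0.4% | Power, 0.6% |
|---|---|---|---|---|
| 60% | 81.0 | 243 | 77.6% | 99.0% |
| 63% | 85.05 | 255 | 79.9% | 99.3% |
| 63.7% | 86.0 | 258 | 80.4% | 99.3% |
| 65% | 87.75 | 263 | 81.4% | 99.4% |
| 70% (pilot) | 94.5 | 283 | 84.5% | 99.7% |

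At 60% the total is 258 − 243 = 15 below the stated minimum (15/258 = 5.8%), or 5 per group. Power for 0.4% is 80 − 77.6 = 2.4 points under the stated figure. With the normal approximation it is 78.5%, or 1.5 points under.

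**Step 4: which rate the 135 fits.** 86/0.65 = 132.3, so 133 per group; 86/0.60 = 143.3, so 144 per group (432 in total). The planned 135 covers 65% but not 60%.

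**The case against.** The best defence is that 60% is a pessimistic case and that the protocol contains several things that work against it.

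- The discount to 60–65% follows directly from the problem of missing medical-record results. Section 4.5 addresses that problem with a staff-guided home HbA1c test, and Section 4.6 pays $20 for it at each of the three time points.
- Section 7.1 analyses the data by intention to treat with a linear mixed model using repeated measures, not a t-test in completers, and this may recover some precision.
- The pilot reached 70%, where 135 per group is more than enough, and the pair 405 and 258 corresponds to a rate inside the stated range.

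All of this bears on how much the error matters, and it stands to that extent. It does not make the stated minimum true. The sample-size paragraph credits neither the home test nor the mixed model. No section gives a revised completion rate, and the gain from the model cannot be computed because the protocol gives no correlation between baseline and follow-up HbA1c.

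A reader might go further and infer that the trial is underpowered, or that it must recruit 432. The documents do not support either inference. The protocol plans on a range and does not single out 60%. Only one of the three contrasts is affected, and at 65% or above the planned number suffices.

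**Conclusion.** Wrong as written, and minor in size. The figure of 258 (86 per group) is not a minimum over 60–65% completion; it requires about 63.7%. At the low end the yield is 243 (81 per group), and power for the 0.4% contrast is 77.6%.

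The required 86 per group is correct. The 0.6% contrast keeps 99% power at 81 per group, and VIDEO+CHW against CONTROL, where the two expected differences sum to 1.0%, keeps more.

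These figures rest on the protocol's own assumptions: SD 0.8%, equal completion in the three arms, an unadjusted t-test, and alpha 0.0167 for each comparison. They say what the paragraph's arithmetic delivers. They do not predict the completion or power that the trial will achieve.

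**What to change.** Replace the yield sentence in Section 3.2 with wording to this effect:

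> At 60–65% completion, 405 yields 243–263 (81 to about 88 per group), giving about 78–81% power to detect 0.4%; 86 per group requires about 64% completion.

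If the sponsor expects the home HbA1c test to lift completion above this range, the paragraph can say so, with the rate assumed and the reason for it.

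The cost is one sentence, and the stated power becomes slightly less favourable at the low end. Enrolment, design and analysis stay as they are.

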### **3.3. Characteristics of the Research Population**

To be eligible for the study, participants must: 1) self-identify as a Chinese immigrant or Chinese American; 2) be above 18 years old, 3) have a diagnosis of T2D in the medical record; 4) have had an appointment with a physician for routine T2D care within the past 12 months; 5) have a most recent  $HbA1c \geq 7\%$ ; 6) be willing to receive brief videos regarding T2D management, and 7) possess a smartphone or, if they do not have one, be willing and able to use a study smartphone. Individuals will be excluded from participation if they meet any of the following: (1) unable or unwilling to provide informed consent; (2) unable to participate meaningfully in the intervention (e.g., uncorrected sight and hearing impairment); (3) unwilling to accept randomization assignment; (4) is pregnant, plans to become pregnant in the next 6 months, or becomes pregnant during the study, or (5) is breastfeeding (e.g., they may have potential dietary restrictions).

## 4. PROCEDURES

### 4.1 Patient Recruitment

Participants will be identified and recruited into the study from NYC health care facilities, including CBWCHC, private practices, community-based organizations, and NYU Langone Health and affiliated provider practices.

We will recruit participants using the following methods:

**a. Posters.** Posters will be placed in NYC health care facilities waiting and examination rooms. Posters will list a contact telephone number that patients can call if interested in enrolling. Posters will also be placed in Chinese community centers (e.g., senior centers) and distributed during Chinese community events.

**b. Direct referral by health care providers.** CBWCHC, NYU Langone Brooklyn site providers, and private practice health care providers will approach patients who are potentially eligible for the study, solicit their interest in the study. If patients express verbal interest in the study participation, their health care providers will share the patient's contact information with the study staff, or patients will also be able to call (self-refer to) to the number provided in the poster and speak with a study staff if they are interested in participating. [name] is the medical director at NYU Brooklyn Family Health Center. We are collaborating with [name] and her team at NYU Brooklyn. They would help refer potential study participants that are eligible and interested in our study. The initial referral list from health care providers will only include patient's name and phone number for those verbally expressed interest in the study. After verbal consent is obtained and documented, the study staff will request the patient's medical information from the medical record.

**c. Electronic Medical Record Search.** We will work with DataCore to generate a report to identify potentially eligible subjects across NYU Langone Manhattan, Brooklyn, and Long Island campuses. Using a query, search will be conducted in EPIC to identify Chinese patients aged 18+ and with type 2 diabetes whose most recent HbA1c value  $\geq 7\%$ . The report will also include demographics including patient name, gender/sex, date of birth, address, phone number, weight, height, BMI, name of primary care physician, most recent HbA1c value and date of measurement. Only the principal investigator and all members of the research team will have access to this report. The report will be generated prior to the recruitment process to help us find potential participants. The report will be kept on a secure electronic NYU research drive to ensure the confidentiality of health information and identifying information from potential participants. These patients will receive a provider letter which will be mailed to them, describing the study and letting them know how they can opt out of further contact. We will permanently delete the report once we meet our recruitment goal. We will replicate similar approaches with CBWCHC and other health care providers, who will perform an electronic medical record search to generate a list of potentially eligible patients at their sites. These patients will receive a provider letter which will be mailed to them, describing the study and letting them know how they can opt out of further contact.

### 4.2 Patient Screening

Upon receiving the referral list (interested patient's name and phone number) from the providers listed above, the NYU bilingual study staff will call the patient and provide more details about the study. If patients expressed interest in participation, the study staff will administer several screening questions over the phone to screen whether or not the participant is eligible (see Telephone Screener).

For patients identified from EPIC and DataCore and electronic medical record search, we will wait 1-2 weeks after the provider letter is mailed out and then call the patients to provide more details about the study. If patients expressed interest in participation, the study staff will administer several screening questions over the phone to screen whether or not the participant is eligible (see Telephone Screener).

Once eligibility is confirmed, the bilingual study staff will send patients via text message a copy of the key information sheet and the verbal consent script schedule a follow up phone call to obtain verbal consent. For those who screened ineligible, we will remove identifiers from the screening data and keep the de-identified data to generate CONSORT diagram for our final manuscript. This is necessary because in the final manuscript, as a researcher, we need to report the recruitment numbers (how many we called, how many we screened ineligible and ineligible reasons). For such purposes, we need to keep de-identified screening data to generate this CONSORT diagram.

### **4.3 Patient Consent**

#### **Written Consent:**

If the participant prefers to provide consent during an in-person visit, we will schedule an in-person visit. A comprehensive written consent form (available in English and Chinese) will be provided to the potential participant. This form will include information about the study purpose, study procedures, potential benefits and risks, data confidentiality, and the participant's rights, including the right to withdraw at any time without any negative repercussions. Participants will be given adequate time to review the consent form before making a decision. They will be encouraged to ask questions and ensure that they fully understand all aspects of the study before signing the consent form. For those who provide written consent, we will measure their weight and height and obtain their demographic information.

#### **Verbal Consent:**

The NYU study staff will make a second phone call to the participant by reading the approved telephone verbal consent. The verbal consent is an accommodation due to the ongoing COVID-19 pandemic in New York, and that the target population for this study is low-income aging immigrants with limited education and low digital literacy. All interventions will be conducted via phone or text message. A waiver of documentation of consent has been requested and approved.

The study team has requested a waiver of signed HIPAA authorization and all HIPAA information will be presented verbally. Under the HIPAA section, we will explain the potential risks of text message. Participants can decide on their own whether they would like to continue to participate.

An IRB-approved verbal consent script will be used and will include the HIPAA information, the subject will verbalize comprehension of the consent form and study enrollment. The date of consent will be documented on the Enrolled Participants Log. The Enrolled Participants Log is the only record linking a participant's name and Subject ID, this information will be kept on a secure electronic drive to ensure the confidentiality of health information and identifying information from participants. Only the principal investigator and all members of the research team will have access to this information.

We will have the verbal consent script available in both English and Chinese. The participant can choose their own preferred language and our bilingual study staff will explain the

study to the participant. The participant will be encouraged to ask any questions they may have before providing the verbal consent.

After verbal consent is obtained, we will schedule third phone call to start baseline study questionnaire survey.

#### **4.4 Baseline Measurement**

During the third phone call, participants will complete a baseline battery of self-report questionnaires. The bilingual study staff will facilitate these assessments and will provide instructions and/or assistance as needed. These phone calls will be audio recorded for data integrity and quality assurance. We will randomly select phone call audio recordings to ensure that they are following our study protocol. Audio recordings will be password protected and stored on the NYU Langone shared drive which is only accessible to our study team members. We will destroy the recordings in July 2029, one year after our grant ends.

##### **4.4.1 Randomization**

The study biostatistician will create a prior randomization sequence using a computer-generated list of random numbers. The independent study staff will inform participants of their group assignment and explain the next step after finishing questionnaires during the baseline phone call.

##### **4.4.2 Intervention Arms**

**Wait-list control group (CONTROL):** Participants in this group will continue to receive the standard of usual care for their T2D at their doctor's office during the course of our study. At the end of the study, the CONTROL group will be provided the opportunity to receive DSMES videos.

**Video-based DSMES (VIDEO):** Participants in the VIDEO group will receive brief pre-recorded DSMES videos, which include both educational and SCT-based behavioral content. All intervention videos have been linguistically and culturally tailored and pilot tested in a prior study. Similar to the prior study, we will deliver video links via text messages. We will send 1 DSMES video each week for a total of 24 weeks with each video lasting about 5 minutes in duration. Our preliminary data demonstrated high feasibility and acceptability of these DSMES videos.

**Video-based DSMES+CHW (VIDEO+CHW):** Participants in this group will receive the same DSMES videos as described above. In addition, they will also receive brief phone calls from CHWs every 2 weeks during the 24 weeks video program. During these calls, CHWs will assess whether participants need assistance on SDOH barriers (e.g., health insurance enrollment, financial assistance on covering medication/test strips, food assistance). If needed, CHWs will link participants to available services within the community. CHWs will also provide assistance on navigating the complex health care systems and serve as an advocate for patients during doctor visits if needed. These phone calls will be audio recorded for data integrity and quality assurance. We will randomly select phone call audio recordings to ensure that they are following our study protocol. Audio recordings will be password protected and stored on the NYU Langone shared drive which is only accessible to our study team members. We will destroy the recordings in July 2029, one year after our grant ends.

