**D4.2. Data Sources and Collection:** 1) To capture data on *utilization patterns* of the intervention, we will extract system files from the RedCap databases every week that have date and time stamps and user logins to assess participation and completion of intervention components. Data will be extracted and analyzed by the NYU research team. 2) At baseline and follow-up, study coordinator will administer *brief surveys* to participating physicians (n=10) to capture data on: satisfaction with workflow before and after intervention, information sources before and after intervention, acceptability of and satisfaction with the integrated intervention, and barriers and facilitators of care coordination tools, building on our prior work. 3) Study coordinator will conduct *qualitative key informant interviews* with physician champion and/or administrators at CBWCHC, community organizations that serve as referral sites, and CHWs (n=15). At baseline, interviews will assess current satisfaction and usage CHW and organizational workflows. At follow-up, the interviews will assess barriers and facilitators to the implementation and adoption process of the integrated intervention, appropriateness, fidelity to the interventions, and to solicit recommendations for the replication and scalability of the intervention to other sites. We will also assess satisfaction and outcomes from the partnership and capacity building process. Questions will be adapted from existing validated measures on acceptability, feasibility, adoption, organizational culture, and scalability and our previous work. 4) We will conduct *fidelity checklists* during CHW biweekly phone calls for the first 2 months to assess that CHWs are covering all the key points outlined in the protocol. A kappa fidelity score will be calculated based on the percentage of key points completed, and provided to the study team. If CHW cannot improve fidelity to > 80% after two months, he/she will not be retained. In addition, CHWs will

keep encounter logs of all interaction with study participants and materials will be reviewed monthly by the study coordinator.

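### VIDEO+CHW participants share community health workers, but the sample size makes no allowance for this and section 7.1 names no CHW term

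*Protocol*

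**What the plan says.** Table 1 in section 3.1 marks the CHW calls for VIDEO+CHW alone. Section 4.4.2 says that in this arm "they will also receive brief phone calls from CHWs every 2 weeks during the 24 weeks video program", which is 24/2 = 12 calls per participant. On these calls the CHW assesses social barriers, links people to services, helps them navigate care and may act as their advocate at doctor visits.

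The data-collection text after Table 2 (D4.2) has CHW fidelity scored against a checklist and adds: "If CHW cannot improve fidelity to > 80% after two months, he/she will not be retained". It also has CHWs keep logs of all their encounters with participants.

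Section 3.2 derives 86 evaluable participants per group "based on a two-sample two-sided t-test", with 80% power, SD 0.8% and "a type I error of 0.0167 (to account for 3 group comparisons"). The difference that drives the number is the smaller of two: "we expect to see a group difference of 0.4% between the VIDEO+CHW and VIDEO groups". For the other adjacent pair, "we expect to observe a 0.6% difference between the VIDEO and CONTROL groups". The section concludes that 405 recruited participants give enough power for all three comparisons.

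Section 7.1 specifies a random effects linear mixed model with repeated measures for Aim 1. It does not define the level of the random effect and does not mention CHWs. The number of CHWs, their caseload, how participants are assigned to them and an ICC appear nowhere in the protocol.

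**The concern.** The CHW component is individual help given by a person over 24 weeks. Participants who share a CHW share whatever that CHW does well or badly, so their outcomes may be correlated. Because this happens in one arm only, the design is partially nested. The mean of the VIDEO+CHW arm then varies more than a calculation for independent participants allows.

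Two things are at stake. If the analysis has no CHW term, both contrasts involving VIDEO+CHW get intervals that are too narrow and a type I error above nominal. If the analysis does have one, the 80% power stated for the 0.4% contrast is not delivered. That contrast measures what CHW support adds to the videos, which section 3.1 gives as a reason for having three arms. A later analysis plan can repair the first problem but not the second, because the sample size is fixed in the protocol.

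**Working it through.** **Inputs from the protocol (3.1, 3.2).** Difference 0.4% for VIDEO+CHW vs VIDEO; 0.6% for VIDEO vs CONTROL, hence 0.4 + 0.6 = 1.0% implied for VIDEO+CHW vs CONTROL; SD 0.8%; two-sided alpha 0.0167; 86 evaluable per arm.

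**Assumptions, not in the protocol.** Number of CHWs K = 3, 5 or 10; within-CHW ICC = 0.01, 0.02 or 0.05; equal caseloads; total SD in the CHW arm kept at 0.8%. The SD comes from the authors' preliminary study, described in 2.1 as a one-arm video pilot with no CHW component, so it cannot be assumed to contain between-CHW variance.

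**Step 1: reproduce the stated figure.** Normal approximation: n = 2 × (2.393 + 0.842)² × (0.8/0.4)² = 83.7, so 84. The exact noncentral t gives 79.9% power at 85 and 80.4% at 86. The stated 86 is therefore correct for independent participants, and it contains no design effect.

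**Step 2: standard error under independence.** SE₀ = 0.8 × √(2/86) = 0.122. Then 0.4/0.122 = 3.279, and normal-approximation power is Φ(3.279 − 2.393) = 81.2%.

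**Step 3: clustering in one arm.**
- Design effect in VIDEO+CHW: DE = 1 + (86/K − 1) × ICC.
- SE ratio: r = √((DE + 1)/2), since only one of the two arms is inflated.
- True type I error if clustering is ignored: 2 × [1 − Φ(2.393/r)].
- Power for 0.4% if clustering is allowed for: Φ(3.279/r − 2.393). The t column uses Satterthwaite degrees of freedom instead.

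Example, K = 3 and ICC 0.05: DE = 1 + 27.67 × 0.05 = 2.38; r = √(3.38/2) = 1.30; error = 2 × [1 − Φ(1.84)] = 6.6%; power = Φ(2.521 − 2.393) = 55%.

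| K | ICC | SE ratio | Error if ignored (nominal 1.67%) | Power if allowed for, normal | Power if allowed for, t |
|---|---|---|---|---|---|
| 3 | 0.01 | 1.07 | 2.5% | 75% | 50% |
| 3 | 0.02 | 1.13 | 3.4% | 69% | 41% |
| 3 | 0.05 | 1.30 | 6.6% | 55% | 25% |
| 5 | 0.01 | 1.04 | 2.1% | 78% | 66% |
| 5 | 0.02 | 1.08 | 2.6% | 74% | 61% |
| 5 | 0.05 | 1.19 | 4.4% | 65% | 48% |
| 10 | 0.01 | 1.02 | 1.9% | 80% | 75% |
| 10 | 0.02 | 1.04 | 2.1% | 78% | 73% |
| 10 | 0.05 | 1.09 | 2.8% | 73% | 67% |

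The error column and the power columns describe different analyses. The test that ignores clustering has power Φ((3.279 − 2.393)/r), which at K = 3 is about 80%, 78% and 75% for the three ICCs.

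**Step 4: the other contrasts.** VIDEO vs CONTROL involves no CHW. At 0.6%, 0.6/0.122 = 4.918 and power is Φ(4.918 − 2.393) = 99%. VIDEO+CHW vs CONTROL at 1.0% in the worst row has 1.0/(0.122 × 1.30) = 6.30, so normal-approximation power is above 99% (about 93% with Satterthwaite degrees of freedom). Its SE ratio and type I error are those in the table.

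**The case against.** Several stronger readings are tempting, and the document does not support them.

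- *Only a handful of CHWs.* No number is given. The nearest figure, 15 interviewees in D4.2, pools champions or administrators, community organizations and CHWs. With 10 CHWs and an ICC of 0.01 the standard error is understated by only about 2%.
- *The analysis treats participants as independent.* Section 7.1 names a random effects model without its levels. A statistical analysis plan, not shown here, could add a CHW effect. The fair statement is that the protocol names no CHW term.
- *The retention rule shows that CHW quality will vary.* It is a contingency within quality control. Checklists, log review and audits of recorded calls should, if anything, reduce variation between CHWs. Coverage of key points is also no evidence about an ICC in HbA1c.
- *The trial suffers inflated error and the lower powers together.* It does not. The error rates belong to an analysis without a CHW term, and the lower powers to one with it.

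These objections limit the size and certainty of the point. They do not remove it: the sizing is written out in 3.2, it holds only for independent participants, and the contrast that sets the number is one that clustering affects.

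**Conclusion.** The point holds conditionally. If the within-CHW ICC is above 0, an analysis without a CHW term understates the standard errors of VIDEO+CHW vs VIDEO and of VIDEO+CHW vs CONTROL. An analysis with one does not reach the stated 80% power for the 0.4% contrast, because 86 per group leaves no room for a design effect. The size depends wholly on two quantities that the protocol does not give: over the assumed grid it runs from negligible (10 CHWs, ICC 0.01) to serious (3 CHWs, ICC 0.05), and at an ICC of 0 nothing changes. The meaningful loss of power is confined to VIDEO+CHW vs VIDEO. For VIDEO+CHW vs CONTROL the issue is the interval and the error rate. VIDEO vs CONTROL is untouched. The plan should be amended on this point, but it does not invalidate the design.

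**What to change.** **Section 7.1.** Specify a partially nested mixed model: a CHW random effect that operates in the VIDEO+CHW arm only, with participants in the other arms as singletons, and small-sample degrees of freedom. Take CHW identity from the existing encounter logs. For analysis, attribute each participant to the first-assigned CHW, so that a change of CHW does not leave the nesting undefined. If there are too few CHWs to estimate the variance, keep one pre-specified primary test and add a sensitivity analysis with standard errors recomputed at fixed ICCs of 0.01 to 0.05. Several fixed-ICC results should not replace the primary test, because that would leave no single decision rule.

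**Section 3.2.** State the planned number of CHWs and restate the power for the 0.4% VIDEO+CHW vs VIDEO contrast as a range over that number and the ICC. The 80% figure belongs to a 0.4% difference and should not be transferred to VIDEO vs CONTROL, which has about 99% at its planned 0.6%.

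**Cost.** A few sentences in two sections and a CHW identifier carried into the analysis file. Randomisation and treatment stay as they are. The price is somewhat wider intervals for the two VIDEO+CHW contrasts, an imprecise variance component if CHWs are few, and a less favourable stated power.
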